#### Primary Analysis

The primary analysis of question order bias will be conducted through regression models in which each outcome in each cluster will be regressed against a dummy variable representing whether each of the other clusters was asked before or after the outcome. For instance, standard drinks consumed in the past week (which is part of Cluster 2), will be regressed against 3 dummy variables, representing Cluster 1, Cluster 3, and Cluster 4, respectively. The dummy variables will take value 0 if the cluster was asked after Cluster 2 and value 1 if the cluster was asked before Cluster 2. For each outcome, 1 regression model will be created, yielding a total of 10 models, using negative binomial regression for counts (outcome 6 and outcome 9), logistic regression for hazardous or harmful drinking (outcome 5, using AUDIT-C scores of 5+ as the cutoff), and normal regression for scores (all other outcomes, possibly log-transformed if found to be skewed).

We will investigate 2- and 3-way interactions among the cluster dummy variables in order to explore if the order of a combination of clusters affects outcomes (eg, if the order of Cluster 1 and Cluster 2 in combination creates a question order bias on the outcomes in Cluster 3).

The proportion of participants abandoning the questionnaire will be analyzed in two ways: (1) using a logistic regression model with allocated arm as a covariate, to identify orders that are more (or less) likely to result in abandonment, and (2) using a logistic regression model with the cluster that was abandoned and the number of questions responded to as covariates, to identify clusters that are more (or less) likely abandoned (adjusted for number of questions responded to).

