### Outcomes

The primary outcomes are the 10 outcomes of the COS measured using the recommended questionnaires [18], and the proportion of participants abandoning the questionnaire.

The secondary outcomes are the proportion of participants visiting the provided links at the end of the questionnaire, and time spent on the questionnaire among completers and abandoners.

The first primary outcome (ie, the responses to the COS) will facilitate the primary analysis of question order effects. As the COS is new, we also wish to measure the abandonment rate in order to guide both future trials utilizing the COS and further development of the COS for online and digital settings.

Measuring the proportion of participants visiting the provided links at the end of the questionnaire is an opportunistic decision to gather some data on the degree to which responding to the COS satisfies participants’ intentions to seek help online. Assessment has been found to affect alcohol outcomes [11,29,30]; thus, differentiation between those who visit the links at the end of the questionnaire with respect to responses to the COS will generate hypotheses for future trials aimed at understanding who is affected by the assessment. The final outcome, time spent on the questionnaire, is captured primarily to guide future research on the anticipated participant burden of completing the COS.

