### Randomization and Blinding

Block randomization (random block sizes of 24 and 48) will be used to achieve equal allocation among arms. The randomization sequence and allocation will be fully automated and computerized. Since no identifiers are collected for individuals, we will use web browser cookies and HTML5 storage to store allocation information on the participants’ web browsers (see Discussion). Participants who have not completed the questionnaire and return to the trial website will be presented with the cluster order according to their assignment. Participants who have completed the questionnaire and return to the trial website will be thanked for their participation, but not offered an opportunity to answer the questions again.

Participants will be aware that they are taking part in a research study; however, the true nature of the study will not be revealed to them, since this would interfere with the effect being studied. Therefore, participants will not be aware of which arm they are in, and hence will be blinded to allocation. Researchers will also be blind to participant allocation.

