### Sample Size

The trial will use a Bayesian group sequential design [35-37] to monitor recruitment, with interim analyses planned for every 50 participants completing the questionnaire. Responses to each of the 10 COS outcomes will be modelled following the primary analyses, and each dummy variable representing cluster order will be assessed for evidence of effect or futility. Let ß_k,i_ represent the coefficients for each dummy variable (i=1,2,3) in each model (k=1...10) and D represent the data available at the interim analyses. Then, the target criteria will be (1) *effect:* p(ß_k,i_ > 0 | D) > 97.5% or p(ß_k,i_ < 0 | D) > 97.5% (ie, if the question order effect is greater or less than 0 with a probability greater than 97.5%); (2) *futility (normal regression):* p(−0.1 < ß_k,i_ < 0.1 | D) > 95% (ie, if the question order effect is close to 0 with a probability greater than 95%); and (3) *futility (negative binomial and logistic regression):* p(log(1/1.2) < ß_k,i_ < log(1.2)) > 95% (ie, if the question order effect is close to 0 with a probability greater than 95%).

For the effect criterion, we will use a skeptical normal prior for dummy covariates (mean 0, SD 1.0), and a wider prior will be used for the futility criterion (mean 0, SD 2.0).

The criteria should be viewed as targets; thus, at each interim analysis, we will evaluate each criterion for each covariate and decide if we believe that recruitment should end. We will only make decisions to stop recruitment entirely, not drop or modify any of the arms. Simulations indicate that we will require a sample size in the range of 1500 to 2500 participants. Recruitment will not exceed 24 months.

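### The second abandonment model uses covariates that are themselves determined by abandonment, so it cannot show which clusters are more likely to be abandoned

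*Protocol article*

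**What the plan says.** The Outcomes section lists the 10 core outcomes "and the proportion of participants abandoning the questionnaire" as primary. Under Primary Analysis, that proportion is analysed with two logistic models.

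- The first is described as "using a logistic regression model with allocated arm as a covariate, to identify orders that are more (or less) likely to result in abandonment".
- The second is described as "using a logistic regression model with the cluster that was abandoned and the number of questions responded to as covariates". Its purpose is "to identify clusters that are more (or less) likely abandoned (adjusted for number of questions responded to").

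Neither the row structure nor the set of people at risk is described for the second model. Three other statements bear on it:

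- Setting and Participants places the end of participation at the point where every question has been answered.
- The Preliminary part of the Analysis section starts from complete cases, takes Bayesian posteriors as the main inference and adds null hypothesis tests at the .05 level.
- Sample Size gives normal priors for dummy covariates, with SD 1.0 for the effect criterion and 2.0 for futility.

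**The concern.** A covariate in a model for abandonment has to be something a participant has before, or independently of, abandoning. Neither covariate here is. The abandoned cluster comes into existence by abandoning, and the number of questions answered records the point at which it happened. A model that conditions on these reproduces the definition of the outcome instead of explaining it.

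At stake is one of the two stated analyses of a primary outcome, and the only one aimed at which cluster drives people away. The Outcomes section wants the abandonment rate in order to guide future trials and further development of the outcome set, and the Introduction invites others to replicate the protocol. An unusable specification could be copied into those studies.

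**Working it through.** **The plan's own figures.** There is no stated figure for abandonment to reproduce. The only design figure is "Simulations indicate that we will require a sample size in the range of 1500 to 2500 participants", and its criteria concern the core outcomes alone: "Responses to each of the 10 COS outcomes will be modelled following the primary analyses". The simulation inputs are not given, but the range is plausible. With the three before/after dummies (pairwise correlation 1/3), Var(β) = 4.8·SD²/n. For an estimate at 0 and the ±0.1 futility band, n = 4.8·(1.96·SD/0.1)², which is 1494, 1844 and 2232 for assumed SDs of 0.9, 1.0 and 1.1. I use 1500 and 2500 below.

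**Separation by definition.** Let K be the number of questions.

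| | Abandoned cluster | Questions answered |
|---|---|---|
| Completer (Y = 0) | none | K |
| Abandoner (Y = 1) | 1, 2, 3 or 4 | at most K − 1 |

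Either column alone predicts Y without error, so the likelihood rises without limit as the coefficients grow. No abandonment rate or item count enters this argument. If questions could be skipped, the second column might overlap, but the first would still separate. If completers are instead coded as missing on the first column, the complete-case rule removes them and Y is constant at 1.

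**Numerical check.** Assumptions: 3, 7, 10 and 17 items in clusters 1 to 4 (K = 37), and a chance of leaving at each question of 0.008 in clusters 1-3 and 0.012 in cluster 4. About 31% then abandon.

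- Completers all had 37 answers; abandoners had at most 36.
- Maximum likelihood failed with a singular matrix at both n = 1500 and n = 2500, with the cluster alone, the count alone, and both together.
- Posterior modes for the four cluster coefficients at n = 1500, by prior SD:

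| Prior SD | Cluster 1 | Cluster 2 | Cluster 3 | Cluster 4 |
|---|---|---|---|---|
| 1 | 3.94 | 4.94 | 4.69 | 5.83 |
| 2 | 6.13 | 6.99 | 6.70 | 7.81 |
| 10 | 11.41 | 12.12 | 11.75 | 12.80 |
| *Abandoners in cluster* | 32 | 79 | 78 | 271 |

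The level is set by the prior. In every row the ranking follows the raw number of abandoners in each cluster, not a rate among those who reached it.

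**No at-risk denominator.** The balanced permutations put each cluster in each position equally often. Even so, the number reaching a cluster depends on how many left in those before it, and a completer passed through all four clusters but enters as a single row labelled none. Adjusting for the final question count does not repair this, because that count is the point of dropout.

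**Recast model, same simulated data.** One row per participant per cluster started; outcome: left during that cluster; covariates: cluster, and questions answered before entering it.

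| | n = 1500: coefficient (SE) | n = 2500: coefficient (SE) |
|---|---|---|
| Cluster 2 vs 1 | 0.91 (0.21) | 0.79 (0.17) |
| Cluster 3 vs 1 | 0.89 (0.21) | 1.31 (0.16) |
| Cluster 4 vs 1 | 2.20 (0.19) | 2.36 (0.16) |
| Prior questions (as share of 37) | −0.36 (0.19) | 0.40 (0.15) |

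It converges with finite coefficients at both sizes.

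**The case against.** Four arguments can be made for the plan.

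1. *Inference is primarily Bayesian with proper priors, so the model can be fitted.* This stands as far as it goes. A reader might infer that the model cannot be estimated at all, or that the posterior is nothing but the prior. Neither is right: a posterior exists, and the data move the coefficients well away from 0. But their size is not identified by the data, and the complementary .05 test has no finite estimate behind it.

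2. *The authors may have meant a person-by-cluster model adjusted for progress, and row structure is a detail an article may omit.* The intention is plausible and fits the stated aim. But the article does not leave the model open. It names the outcome as the proportion abandoning and names the covariates, and the abandoned cluster is not the same variable as the cluster currently being answered.

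3. *Design and stopping are unaffected.* This stands. The interim criteria cover only the 10 core outcomes.

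4. *The first abandonment model is sound.* This also stands. A reader might infer that a 24-level arm factor wastes the factorial design. The documents do not support that. An order is an arm, so the covariate matches the aim of identifying orders; the model is estimable; and pooled contrasts can be formed from its coefficients. The before/after dummies of the other primary models do not carry over directly, because they are defined relative to the cluster an outcome belongs to and abandonment belongs to none.

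What remains for the first model is precision for single orders. With equal allocation ("Block randomization (random block sizes of 24 and 48) will be used to achieve equal allocation among arms") there are 1500/24 = 62.5 to 2500/24 ≈ 104 participants per arm. At an assumed 30% abandonment and N = 1500, the SE of an arm-versus-arm log odds ratio is √(2/(62.5·0.21)) = 0.39. In a model with the six pairwise-order indicators, enumeration of the 24 orders gives a variance of 7.2/(N·p(1−p)), so the SE is √(7.2/(1500·0.21)) = 0.15. The ratio is √(48/7.2) = 2.58. The two quantities answer different questions, so this supports a supplement and is not an error in the plan.

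**Conclusion.** The second abandonment model is wrong as written and must be changed. It is a stated analysis of a primary outcome, and if followed literally it cannot meet its stated aim. The separation is complete and rests only on the definitions of the two covariates and of completion. The prior-dependence (coefficients of about 4-6, 6-8 and 11-13 for prior SDs of 1, 2 and 10) and the standard errors of the recast model rest on assumed item counts and abandonment rates and are illustrative.

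The finding does not extend to the first abandonment model, the 10 core-outcome models, the sample size or the stopping criteria.

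**What to change.** Replace the second abandonment model with a discrete-time logistic model:

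- one row per participant per cluster started;
- outcome: abandoned during that cluster, yes or no;
- covariates: current cluster (4 levels), and either its position or the number of questions answered before entering it.

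State also whether the target is the chance of leaving per cluster or per question. Clusters differ in length, and in the simulation clusters 1 to 3 had the same chance per question yet differed per cluster. One row per question gives the per-question version.

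Optionally, report pooled contrasts (six pairwise-order indicators, or cluster by position) beside the 24-arm model, noting that a main-effects version assumes the orderings do not interact.

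The cost is a change of wording and a reshaping of response data the trial collects anyway. No new data, arms or participants are needed.

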#### Secondary Analysis

The proportion of participants visiting the provided links at the end of the questionnaire will be analyzed using a logistic regression model with the COS outcomes as covariates under both standard normal priors and shrinkage priors [34].

Time spent (in seconds) on the questionnaire will be reported among completers and abandoners and analyzed in two ways: (1) using normal regression with arm as a covariate (completers and abandoners, possibly log-transformed) and (2) using normal regression with the COS outcomes as covariates (completers only, possibly log-transformed). Both analyses will be conducted under standard normal priors, and the second analysis will also be conducted using shrinkage priors [34].

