However, the variety of outcome measures used in trial evaluations of ABIs’ effectiveness and efficacy is a limiting factor in evidence synthesis across all modes of intervention delivery (eg, face-to-face and online). Comparisons across trials and synthesis of outcomes as evidence are sometimes impossible despite the use of similar interventions. The ORBITAL (Outcome Reporting in Brief Intervention Trials: Alcohol) project [14] was established to overcome this issue through the determination of an international, consensus-derived core outcome set (COS). The aim was to prioritize the key outcomes to be measured in all online, digital, and otherwise delivered ABIs designed for adult drinkers who are at risk or currently experiencing harm, but who are not seeking treatment. This consensus was derived using the established COMET (Core Outcome Measures in Effectiveness Trials) Methodology [15], including a systematic review that quantified the diversity in outcomes and measurement reporting on 2641 different outcomes, measured in 1560 different ways, in 405 trials of ABIs [16]. This was followed by two e-Delphi (online method to reach consensus) rounds [17], a consensus meeting, and psychometric evaluation to decide the final COS and how outcomes should be measured [18]. The COS established 10 outcomes, which are (1) frequency of drinking, (2) typical number of drinks consumed on a drinking day, (3) frequency of heavy episodic drinking, (4) combined consumption measure, (5) hazardous or harmful drinking, (6) standard drinks consumed in the past week, (7) alcohol-related consequences, (8) alcohol-related injury, (9) use of emergency health care services, and (10) quality of life.

The first 5 outcomes in the COS are measured using the WHO’s Alcohol Use Disorders Identification Test - Consumption (AUDIT-C) tool [19]. Outcome 4 is measured by the total AUDIT-C score, and for outcome 5 a clearly outlined and justified cutoff point of the AUDIT-C score suitable for the country and population should be used. Outcome 6 is measured by asking how many standard drinks were consumed each day of the last week and reported in grams to allow for intercountry comparison.

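### The link-visit and time models enter the AUDIT-C total together with the three items it sums, so the separate coefficients of outcomes 1 to 4 are not identified

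*Protocol article*

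**What the plan says.** All references are to the protocol article.

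- **Secondary Analysis, link visits.** The proportion visiting the links "will be analyzed using a logistic regression model with the COS outcomes as covariates under both standard normal priors and shrinkage priors".
- **Secondary Analysis, time spent.** The second of two time analyses is done "using normal regression with the COS outcomes as covariates", among completers. On priors: "Both analyses will be conducted under standard normal priors, and the second analysis will also be conducted using shrinkage priors".
- **Introduction, outcomes.** There are ten outcomes. "The first 5 outcomes in the COS are measured using the WHO’s Alcohol Use Disorders Identification Test - Consumption (AUDIT-C) tool". Within that group, "Outcome 4 is measured by the total AUDIT-C score".
- **Primary Analysis.** Outcome 5 is a cutoff of the same score (5 or more). Outcomes 1 to 4 are treated as scores.
- **Analysis, Preliminary.** Parameters are to be read from their marginal posteriors, with null hypothesis tests at the .05 level as a complement.

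No outcome is excepted from the covariate set, and nothing says that the outcomes enter one at a time.

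**The concern.** A regression cannot separate the effect of a total from the effects of the parts that make it up. If all COS outcomes enter one model, the coefficients of outcomes 1 to 4 can be shifted against one another without changing the fit. Yet the plan reads each coefficient from its own marginal posterior.

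The Outcomes section says the link-visit analysis should show how visitors differ in their COS responses and so generate hypotheses for later trials. A real association with AUDIT-C drinking could be spread over four wide posteriors and pass for no association. The Bayesian fit would give no warning, because proper priors keep the posterior proper.

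**Working it through.** The plan states no figure for these models, so there is none to reproduce. The check is algebra on its definitions, followed by a simulation.

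**Inputs.** The covariates are the ten COS outcomes, and the priors are standard normal (Secondary Analysis). Outcome 4 is the AUDIT-C total (Introduction). The upper end of the planned sample is 2500 (Sample Size). Two readings are assumed: the total is the plain sum of the three item scores, which the article implies but does not write out, and outcomes 1 to 4 enter untransformed.

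**Step 1: what the data can identify.** Write O1 to O4 for the outcomes and b1 to b4 for their coefficients. With O4 = O1 + O2 + O3,

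b1·O1 + b2·O2 + b3·O3 + b4·O4 = (b1+b4)·O1 + (b2+b4)·O2 + (b3+b4)·O3.

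The likelihood depends on the three sums only. It is flat along d = (1, 1, 1, −1)/2. With an intercept and ten outcomes, the design matrix has 11 columns and rank 10. This concerns the covariates alone, so it holds for both models, whether or not time is log-transformed.

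**Step 2: the floor on the posterior SDs.** Under independent N(0,1) priors, the component along d is independent of the rest a priori and the data do not touch it. Its posterior is its prior: mean 0, SD 1. Each of b1 to b4 has weight ±1/2 on d, so

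Var(bj | data) ≥ (1/2)² × 1² = 0.25, that is, SD ≥ 0.5 at any n.

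On standardised covariates the weights are proportional to the SDs of the four scores. The floors then depend on the item correlations, but they are not zero. Uncorrelated items of equal variance give 1/√6 = 0.41 for each item and 1/√2 = 0.71 for the total.

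**Step 3: simulation.** COS data were generated from assumed distributions with correlated items and about 13% visiting the links. The fit was a penalised logistic model with a Laplace posterior. On the raw scale with N(0,1) priors:

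| n | SD of b1, b2, b3, b4 | SD of b1+b4, b2+b4, b3+b4 | SD of b1, b2, b3 without outcome 4 |
|---|---|---|---|
| 1500 | 0.51, 0.51, 0.51, 0.50 | 0.111, 0.086, 0.096 | 0.111, 0.086, 0.096 |
| 2500 | 0.51, 0.50, 0.51, 0.50 | 0.086, 0.068, 0.078 | 0.086, 0.068, 0.078 |
| 100,000 | 0.50, 0.50, 0.50, 0.50 | 0.014, 0.011, 0.012 | 0.014, 0.011, 0.012 |

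- With a prior SD of 2, the SDs of b1 to b4 become 1.00, while those of the sums hardly move.
- On standardised covariates, the SDs of b1 to b4 at n = 100,000 are 0.28, 0.35, 0.35 and 0.82, and they double with a prior SD of 2.
- The coefficient of outcome 5 is learned: SD 0.28 at n = 2500 and 0.046 at n = 100,000.

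**Step 4: what a reader of the marginals would see.** Suppose the log-odds rise by s per AUDIT-C point through the total. The three sums then settle at s. The prior picks the split that minimises 3(s − b4)² + b4², so 8·b4 = 6s, giving b4 = 0.75s and 0.25s for each item. A 95% interval for b4 excludes zero only if 0.75s > 1.96 × 0.5 = 0.98, so s > 1.31, an odds ratio of about 3.7 per point.

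For an assumed odds ratio of 1.22 per point, s = 0.199. The interval for b4 centres on 0.149 and runs from −0.83 to 1.13. Without outcome 4, each item coefficient would be near 0.199 with an SD of 0.068 to 0.086 at n = 2500, which is 2.3 to 2.9 SDs from zero.

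**The case against.** The strongest reply is that little is lost. Only one direction in four is unidentified, and whether an effect belongs to a total or to its own items is hardly a meaningful question. The three sums are estimated well, and the posterior means of b1 to b4 respond to the data through them. All of that stands. It does not rescue the plan as written, because the plan reads separate marginal posteriors and not those sums.

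The planned shrinkage priors are a second reply. The result that the flat direction keeps exactly its prior holds for independent normal priors of equal variance. Under a non-normal shrinkage prior, the data can inform that direction indirectly through the sums. This limits Step 2 to the standard normal analyses. The split still rests on the shape of the prior, because the likelihood carries no information about it.

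Third, log-transforming outcome 4 alone would restore full rank (11 of 11 in the simulation). The article mentions a log transform of scores only where they are the response and are skewed.

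A reader might go further and infer that all AUDIT-C coefficients come from the prior, that the models say nothing about drinking, or that the planned tests fail altogether. The documents do not support this. Outcome 5 is a threshold, not a linear combination, and is identified. Outcome 6 (past-week drinks) and outcomes 7 to 10 are untouched, as are predictions. Tests of outcomes 5 to 10, of the three sums and of the AUDIT-C block remain available. Only the individual maximum-likelihood tests of outcomes 1 to 4 cannot be computed without dropping a term.

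**Conclusion.** The point holds in limited form. As stated, the covariate set of both secondary models leaves the separate coefficients of outcomes 1 to 4 unidentified. With standard normal priors on raw scores, their posterior SDs cannot fall below 0.5 however many participants are recruited.

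The algebra rests on the total being the plain sum of the items and on all four entering one model untransformed. The comparison figures of 0.07 to 0.09 at n = 2500 also rest on assumed data distributions and an assumed link-visit rate. The simulation covers the logistic model; for the time model the argument is the algebra alone.

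The severity is minor. Both analyses are secondary: one is described as opportunistic and hypothesis-generating, the other as guidance on participant burden. The primary models use each outcome as the response, so they and the stopping criteria are not affected.

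**What to change.** In Secondary Analysis, state that outcome 4 is left out of both models and outcomes 1 to 3 are kept. This loses no linear information: the item coefficients then equal the sums that the full model identifies. If an effect of the total is wanted, fit a separate model with outcome 4 in place of outcomes 1 to 3, and say that it assumes equal effects per point for the three items. Outcome 5 need not be removed. The cost is one or two sentences, with no change to data collection, sample size or the primary analysis.

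### The time regressions fix a standard normal prior but leave the outcome scale open between seconds and log seconds; on seconds that prior would erase any realistic difference between question orders

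*Protocol article*

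**What the plan says.** The Secondary Analysis section of the protocol names the unit and announces two models: "Time spent (in seconds) on the questionnaire will be reported among completers and abandoners and analyzed in two ways". The first is described as "using normal regression with arm as a covariate (completers and abandoners, possibly log-transformed"). The second regresses time on the COS outcomes among completers, with the same optional log transform. The priors follow: "Both analyses will be conducted under standard normal priors, and the second analysis will also be conducted using shrinkage priors". The section does not say what would trigger the log transform, that time is standardised, or that the prior is rescaled to the outcome.

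Three other places matter:
- The Outcomes section lists time as a secondary outcome and says that "time spent on the questionnaire, is captured primarily to guide future research on the anticipated participant burden of completing the COS".
- The Preliminary analysis section makes marginal posterior distributions the basis for interpreting estimates, with null hypothesis tests at the .05 level as a complement.
- The Sample Size section uses a prior of the same width for the primary order effects and calls it skeptical: "we will use a skeptical normal prior for dummy covariates (mean 0, SD 1.0").

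**The concern.** A prior with SD 1 has no fixed strength; its strength depends on the unit of the outcome. On log seconds, a coefficient of 1 means one order takes about 2.7 times as long as another, so the prior is wide. On seconds, the same prior says before any data that question orders are very unlikely to differ by more than about 2 s. The plan allows either scale.

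If the seconds scale were used, the posterior for each between-order contrast would be little more than the prior: a mean near zero and a credible interval about 4 s wide, whatever the size of a plausible true difference. That interval would look like precise evidence of no difference. Since the plan interprets estimates through their posteriors, a reader planning a trial around participant burden could conclude that cluster order does not affect completion time when the data had hardly been used.

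**Working it through.** **Inputs from the protocol.** 24 arms with equal allocation (Abstract; Randomization and Blinding). Sample size: "Simulations indicate that we will require a sample size in the range of 1500 to 2500 participants". So n = 1500/24 = 62.5 to 2500/24 = 104.2 per arm. Prior: Normal(0, 1) on the coefficients.

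**Assumptions.** The protocol gives no SD for time. I take 100 to 400 s, with 30 s as a deliberately small value, and SD 0.5 to 0.8 on the log scale. The true state is one order 60 s longer than the rest.

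**The plan's own figure.** The protocol gives no figure for the time analysis. The 1500 to 2500 range is used only as an input. It cannot be strictly reproduced because the simulation inputs are not given. It is plausible for the normal-regression futility rule: with an assumed outcome SD of 1, N = 4/(0.1/1.96)² = 1537, or 1844 after a variance inflation of 1.2 for the correlation of 1/3 between order dummies.

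**Model 1 on seconds.** Flat intercept, 23 arm dummies each with a Normal(0, 1) prior. Let a = n/SD², the data precision of one arm mean relative to the prior precision of 1. Then

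posterior mean = 60 × [a/(1 + a)] × [1 − 1/(24 + a)].

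The last factor arises because the one longer arm also pulls the intercept.

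For example, with N = 1500 and SD 100 s: a = 62.5/10000 = 0.00625, so 60 × 0.00621 × 0.958 = 0.36 s.

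| SD of time | N | a | Posterior mean | 95% interval | Unpenalised SE of a contrast, SD × √(2/n) |
|---|---|---|---|---|---|
| 100 s | 1500 | 0.00625 | 0.36 s | -1.60 to 2.31 s | 17.9 s |
| 100 s | 2500 | 0.01042 | 0.59 s | -1.36 to 2.54 s | 13.9 s |
| 400 s | 1500 | 0.00039 | 0.02 s | -1.94 to 1.98 s | 71.6 s |
| 400 s | 2500 | 0.00065 | 0.04 s | -1.92 to 2.00 s | 55.4 s |
| 30 s | 1500 | 0.0694 | 3.7 s | 1.84 to 5.63 s | 5.4 s |
| 30 s | 2500 | 0.1157 | 6.0 s | 4.11 to 7.83 s | 4.2 s |

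The posterior SD is 0.995 to 1.000 s for SDs of 100 to 400 s, so the interval is essentially the prior's own. Every interval in the table excludes 60 s. The posterior mean falls below 1 s once the SD of time reaches about 60 s (N = 1500) or 77 s (N = 2500).

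Model 1 also includes abandoners, so n could exceed these values if 1500 to 2500 counts completers. Doubling the larger n does not change the picture: at SD 100 s, a = 208.3/10000 = 0.0208, and 60 × 0.0204 × 0.958 = 1.2 s.

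**Model 1 on log seconds.** The fraction kept is the same expression without the 60.
- SD 0.8, N = 1500: a = 62.5/0.64 = 97.7; 0.9899 × 0.9918 = 98.2%.
- SD 0.5, N = 2500: a = 104.2/0.25 = 416.7; 0.9976 × 0.9977 = 99.5%.

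**Model 2, time on COS outcomes.** Treat the covariates as uncorrelated and give each an SD of 1, so that covariate units play no part. The fraction kept is 1/(1 + SD²/N).
- Seconds, SD 100, N = 2500: 1/(1 + 4) = 20%.
- Seconds, SD 400, N = 1500: 1/(1 + 106.7) = 1%.
- Log seconds, SD 0.8, N = 1500: 1/(1 + 0.00043), over 99.9%.

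**The case against.** The strongest reply is that the authors would very probably log the times. Durations cannot be negative and are usually skewed, and the Primary Analysis section ties its own optional log transform to skewness, so the same reading is natural here. The most extreme figures, at an SD of 400 s, belong to the case where logging is likeliest. This stands as a judgement of what would probably happen, and it is why the point is conditional. It does not remove the point: the time models state no trigger, and an analysis in seconds would comply with the text.

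A reader might infer that the plan commits to seconds, so that a one-minute difference would certainly be reported as under one second. The text does not support that: both time models carry the log option. The under-one-second result also needs an SD of time above roughly 60 to 77 s in the joint model, which is an assumption, though a modest one.

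Nor would every time result be lost. The .05 tests involve no prior, and the plan also says that "Time spent (in seconds) on the questionnaire will be reported among completers and abandoners", which speaks directly to participant burden. Both limit the harm. They do not repair the posteriors, and a significant test beside an interval tight around zero would leave the reader with an unexplained conflict.

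A further inference would be that COS covariates enter in raw units and are therefore shrunk according to their unit, both in the second time model and in the link-visit model, described as a "logistic regression model with the COS outcomes as covariates under both standard normal priors and shrinkage priors". The article does not say whether covariates are scaled. That is the kind of detail an article may leave to fuller documents or to the model code it promises to host openly. The form of the shrinkage prior rests on a cited source that is not at hand. No claim is made on either.

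**Conclusion.** The point holds conditionally. The prior is fixed while the scale is not, and the two permitted scales give opposite answers: on log seconds the prior keeps 98% to 99.5% of a between-order effect, and on seconds it keeps at most about 1% (0.59 of 60 s) for SDs of 100 to 400 s, with a falsely narrow interval. The SDs are assumed, but even at 30 s the posterior mean is only 3.7 to 6.0 s and 60 s is excluded. The regression on COS outcomes has the same exposure through the scale of time alone.

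This is a minor-to-moderate matter. Time is a secondary outcome, plays no part in stopping recruitment or in the sample size, and does not bear on the primary order-effect conclusions.

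**What to change.** In the Secondary Analysis section, replace the optional log transform of time with a fixed rule: time is analysed as log(seconds) in both regressions, under the stated priors, and effects are reported as time ratios. Dividing time by its SD before the standard normal prior is applied would serve as well: on that scale a = n, and the prior keeps over 96% of a contrast (62.5/63.5 × [1 − 1/86.5] = 97% at N = 1500).

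As an optional clarification, state whether the COS covariates are centred and scaled before the priors are applied.

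The cost is one or two sentences. Results are then read as ratios or SD units rather than seconds; the descriptive times can still be given in seconds. Data collection, design and sample size do not change.
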